#### Secondary outcome measures

##### PTSD Checklist for DSM-5

The severity of PTSD complaints will be assessed with the 20-item PTSD Checklist for DSM-5 [47, 48]. This measure is adapted from the PTSD Checklist for DSM-IV and is in accord with the criteria of PTSD of the DSM-5. Respondents are asked to rate to what extent they experienced PTSD symptoms during the last month on a 5-point scale ranging from 0 (“not at all”) to 4 (“extremely”). A total score (range 0–80) will be obtained by summing item-scores. The initial psychometric properties of the PTSD Checklist for DSM-5 are good [49]. We adapted the wording “the stressful experience” in the instruction and the items to “the events that are associated with the disappearance” (e.g., “In the past month, how much were you bothered by repeated, disturbing, and unwanted memories of the events that are associated with the disappearance?”). The PTSD Checklist for DSM-5 will also be used to screen for eligibility in the first part of the screening procedure (see Fig. 1). The provisional cut-off score of >38 or the diagnostic rule of scoring at least a 2 (“moderately”) on at least 1 cluster B item, 1 cluster C item, 2 cluster D items, and 2 cluster E items will be used as inclusion criteria [48].

##### Inventory of Depressive Symptomatology—Self-report

The severity of depressive symptoms will be assessed with the 30-item Inventory of Depressive Symptomatology—Self-report [50, 51]. Descriptions of depressive symptoms are provided (e.g., *“Feeling sad”*) and respondents are asked to choose an answer that best describes how they felt during the last week (e.g., “I feel sad nearly all of the time”). The items are presented as multiple-choice items, with four options. Total score ranges from 0 to 84 and will be obtained by summing up 28 of the 30 items. This widely used measure has good psychometric properties [51]. The Inventory of Depressive Symptomatology—Self-report will also be used to screen for eligibility in the first part of the screening procedure (see Fig. 1), whereby a score of >13 is defined as an indication of mild depression [52, 53].

##### Southampton Mindfulness Questionnaire

Extent of mindfulness will be assessed with the 16-item Southampton Mindfulness Questionnaire [54, 55]. This instrument is specifically developed to assess changes in the ability to respond mindfully to distressing thoughts and images [54], which are key elements of the treatment (e.g., “Usually when I experience distressing thoughts or images I am able just to notice them without reacting”). Respondents are asked to rate their agreement with each item on a 7-point scale ranging from 0 (“totally agree”) to 6 (“totally disagree”). After reverse coding of some items, a total score (range 0–96) will be obtained by summing the scores for each item. The instrument showed adequate psychometric properties [54].

#### Potential mediators

##### Self-Compassion Scale

The extent of self-compassion will be assessed with the Self-Compassion Scale [56]. The Dutch version of the Self-Compassion Scale consists of 24 items [57] instead of the 26 items in the original version. Respondents are asked to rate how often they behave in the stated manner on a 7-point scale (instead of a 5-point scale in the English version) with anchors “almost never” and “almost always” (e.g., “When I’m feeling down I tend to obsess and fixate on everything that’s wrong”). After reverse coding of some items, the total score (range 24–168) will be obtained by summing all items. The instrument showed adequate psychometric qualities [56].

##### Trauma Memory Questionnaire

The Trauma Memory Questionnaire consists of 13 items divided over two subscales, namely intrusion and disorganization [58, 59]. Only the 8-item intrusion subscale will be administered in this study. We adapted the words that refer to “death” to “disappearance” (e.g., “My memories of the disappearance consist of vivid images”). The items represent different characteristics of intrusive memories associated with the disappearance. Respondents are asked to rate their agreement with each item on a scale ranging from 0 (“not at all”) to 4 (“very strongly”). The original and translated version showed both adequate psychometric properties [58, 59].

##### Grief Cognition Questionnaire

Negative cognitions associated with the disappearance will be assessed with four subscales of the Grief Cognition Questionnaire [60]. We adapted the wording of the items by referring to the disappearance instead of death. The subscales represent negative beliefs about the self (six items, e.g., “Since he/she has been missing, I feel less worthy”), life (four items, e.g., “My life is meaningless since he/she has been missing”), the future (five items, e.g., “I don’t have confidence in the future”) and one’s own grief reactions (four items, e.g., “Once I would start crying, I would lose control”). Respondents rate their agreement with each item on 6-point scales with anchors “disagree strongly” and “agree strongly”. Psychometric properties of this measure are adequate [60].

##### Depressive and Anxious Avoidance in Prolonged Grief Questionnaire

The extent of avoidance behaviour will be assessed with the 9-item Depressive and Anxious Avoidance in Prolonged Grief Questionnaire [61]. As with the other measures, we adapted the words that refer to “death” to “disappearance”. Five items represent depressive avoidance (“I avoid doing activities that used to bring me pleasure, because I feel unable to carry out these activities”) and four items represent anxious avoidance (“I avoid situations and places that confront me with the fact that he/she has been missing and possibly may never return”). Participants rate their agreement with each item on a 6-point scale with anchors “not at all true for me” to “completely true for me”. Psychometric properties of the subscales are adequate [61].

##### Perseverative Thinking Questionnaire

The Perseverative Thinking Questionnaire is a 15-item measure to assess the severity of content-independent repetitive negative thinking [62, 63]. This measure represents the key features of repetitive negative thinking, the perceived unproductiveness of repetitive negative thinking, and the mental capacity that is captured by repetitive negative thinking. Respondents will be asked to rate each item on a 5-point scale ranging from 0 (“never”) to 4 (“almost always”) (e.g., “My thoughts repeat themselves”). The Dutch translation yielded adequate psychometric properties similar to those of the original German and English versions [62, 63].

##### Ruminative Response Scale

The brooding subscale of the Ruminative Response Scale will be administered to measure the tendency to ruminate [64, 65]. Brooding represents a dysfunctional style of depressive rumination [64]. The respondents are instructed to rate what they generally do or think when they feel sad. Respondents will be asked to rate each of the 5 items on a 4-point scale ranging from 1 (“almost never”) to 4 (“almost always”) (e.g., “I think Why do I always react this way?”). Psychometric properties of this measure are adequate [64, 66].

#### Measures used for monitoring treatment progress per session

##### Self-Compassion Scale—Short Form

The 12-item Self-Compassion Scale—Short Form [67] is a shortened version of the Self-Compassion Scale [56]. The Self-Compassion Scale—Short Form consists of two items of each of the six subscales of the extended version. A specific time frame (“the past 7 days”) was added to the instructions in order to monitor the changes in current self-compassion session by session. Psychometric properties of this measure are good [67].

##### Repetitive negative thinking visual analogue scale

We developed the following item to assess the frequency of repetitive negative thinking: “In the past 7 days, to what extent have you been bothered by repeated negative thoughts related to the disappearance of your loved one?”. The item is rated on a visual analogue scale.

##### Characteristics of intrusive memories and images

Six items were developed to assess characteristics of intrusive memories or images during the past 7 days, based on the Intrusive Memory Interview [68]. The first two items assess the content of a recurrent and unwanted memory or image related to the disappearance that was most bothering during the preceding 7 days. First, the participant is asked to write down the content of this memory or image in five key words. Second, the participant is asked to indicate whether the memory or image represents something that “actually”, “possibly”, or “did not happen”. The other four items consist of visual analogue scales that assess the following characteristics of the intrusive memories or images: the extent of distress associated with it, the degree to which they appear to happen in the present, frequency, and vividness (e.g., “How vivid were the intrusions?”).

#### Other measures

Sociodemographic variables (e.g., gender, date of birth, and educational level) of the participants and missing persons will be registered at the first measurement occasion. The number of sessions the participants attended will be registered at the 1-week post-treatment assessment. In case the participant attended less than eight sessions, the reason(s) for drop-out will be registered. The following two open-ended questions regarding the evaluation of the treatment will also be administered at the 1-week post-treatment assessment: “About which aspects of the treatment are you satisfied?” and “About which aspects of the treatment are you less satisfied?”. The questionnaires and time points are summarised in Table 1.

**Table 1 Tab1:** Overview of variables, concepts, measures, and time points

Variable	Concept	Measure	Time points
Primary outcome measures	Severity of PCBD symptoms	ICG	T0, T0.1, T1, FU1, FU2
Secondary outcome measures	Severity of PTSD symptoms	PCL-5	T0, T0.1, T1, FU1, FU2
	Severity of depressive symptoms	IDS-SR	T0, T0.1, T1, FU1, FU2
	Extent of mindfulness	SMQ	T0, T0.1, T1, FU1, FU2
Mediator	Severity of grief cognitions	GCQ	T0, T0.1, T1, FU1, FU2
	Severity of rumination	RRS	T0, T0.1, T1, FU1, FU2
	Severity of repetitive negative thinking	PTQ	T0, T0.1, T1, FU1, FU2
	Ability to be self-compassionate	SCS	T0, T0.1, T1, FU1, FU2
	Severity of intrusive memories	TMQ	T0, T0.1, T1, FU1, FU2
	Severity of avoidance behaviour	DAAPGQ	T0, T0.1, T1, FU1, FU2
Process of change session by session	Ability to be self-compassionate	SCS-SF	Start of each treatment session
	Severity of intrusive memories and images	Intrusive memories and images vas	Start of each treatment session
	Frequency of repetitive negative thinking	RNT vas	Start of each treatment session
Other variables	Sociodemographic information		T0
	Evaluation of the treatment and reason(s) for drop-out		T1

*ICG* Inventory of Complicated Grief, *PCL-5* Posttraumatic Stress Disorder Checklist for DSM-5, *IDS-SR* Inventory of Depressive Symptomatology—Self-Report, *SMQ* Southampton Mindfulness Questionnaire, *GCQ* Grief Cognition Questionnaire, *RRS* Ruminative Response Scale, *PTQ* Perseverative Thinking Questionnaire, *SCS* Self-Compassion Scale, *TMQ* Trauma Memory Questionnaire, *DAAPGQ* Depressive and Anxious Avoidance in Prolonged Grief Questionnaire, *SCS-SF* Self-Compassion Scale – Short Form, *RNT vas* Repetitive Negative Thinking visual analogue scale, *T0* baseline measure, *T1* post-treatment assessment, *T0.1* post-waiting period measure, *FU1* follow-up measure 1, *FU2* follow-up measure 2

#### Treatment

The treatment is manualized and consists of eight 45-min individual face-to-face therapy sessions offered in a period of maximally 12 weeks. The treatment protocol draws from CBT for treatment of PCBD [23, 69]. Participants learn cognitive behavioural skills and mindfulness practices that enable them to disengage from dysfunctional cognitive patterns related to their missing loved one, both during the sessions and through homework assignments.

In the first session, the therapist and client introduce themselves, exchange expectations regarding the treatment, and the participant is invited to share his/her story about the disappearance of the loved one. The participant receives a manual (containing psycho-education, writing assignments, and exercises for how to handle maladaptive thoughts). Social support is the theme of the second session. The client is asked to invite a relative to join the client in the second session. Mindfulness exercises are introduced in session 3. The therapist explains that mindfulness training consists of sustained attention focused on the body and breath, which integrates a decentred view of thoughts as passing mental events (i.e., “rather than simply being their emotions, or identifying personally with negative thoughts and feelings, patients relate to negative experiences as mental events in a wider context” (p. 276) [70]). A mindfulness exercise is practiced, and the participant will be encouraged to perform mindfulness exercises at home at least five times a week from therapy session 3 to 8. The mindfulness exercises [71] that stem from mindfulness-based cognitive therapy [31] are offered on the website of our research program (www.levenmetvermissing.nl) and via a CD-ROM. The participant is asked to report aspects of their mindfulness-experiences in a mindfulness-diary (e.g., which exercise, duration of the exercise, experiences with the exercise). During session 4 to 8, CBT will be applied that consists of cognitive restructuring and exposure interventions. Cognitive restructuring aims to change dysfunctional thought patterns, and exposure techniques aim to reduce anxiety and avoidance behaviour. Four structured writing assignments are added in a fixed order to the protocol for three reasons. Firstly, the assignments can serve as exposure assignment (e.g., in one of the writing assignments participants are instructed to write about their deepest thoughts and feelings associated with the most stressful memory or image related to the disappearance that keeps popping into their mind) [72]. Secondly, the assignments can increase awareness of inner thoughts and feelings [73, 74]. Lastly, writing about traumatic experiences helps to keep the therapeutic process flowing between the sessions [75]. Two of the writing assignments are imaginary exposure-assignments encouraging participants to tolerate thoughts and feelings related to the disappearance. The first assignment (between session 1 and 2) addresses the impact of the disappearance. The participant is instructed to write about the most intense thoughts and feelings during the first days of the disappearance, followed by a description of how his/her life was before the disappearance and the most painful consequences of the disappearance on his/her life. The second assignment (between session 2 and 3) addresses the description of an image or memory related to the disappearance. The participant is invited to write about the most painful image or memory related to the disappearance and to describe all experiences (thoughts, feelings, and sensations) that come to his/her mind while thinking about that image or memory in as much detail as possible. The third writing assignment (between session 4 and 5) consists of writing a supportive letter to a hypothetical friend that is facing the same situation. This assignment aims to promote the development of new perspectives on the disappearance and its circumstances and to challenge dysfunctional thoughts and behaviour patterns. In the fourth writing assignment (between session 7 and 8), the participant is instructed to write about what he/she has learned during the treatment and how he/she dealt with the disappearance prior to treatment, how he/she deals with it at the moment, and how he/she wishes to deal with it in the future. This final assignment aims to foster empowerment of the participant, in order to deal with possible difficulties in the future. The same sort of writing assignments has been successfully used in treatments of PTSD and PCBD [76, 77].

A group of qualified therapists has received an 8-h training to apply the treatment protocol. The first, third, and last author offered the training. The therapists are all governmentally licensed as psychotherapists or mental healthcare psychologists. They are all part of a network of trained therapists divided over the Netherlands and are experienced in the treatment of PCBD, MDD, and PTSD as a result of extraordinary, high impact loss-related situations.

#### Treatment fidelity

Treatment fidelity will be monitored by asking the therapists to report all compliances and deviations from the treatment protocol in a journal. In addition, supervision takes place every month. Participants are asked to send the writing assignments and mindfulness-diary to the first author at the end of each treatment in order to monitor the compliance.

#### Analyses

##### Feasibility analyses

Analyses regarding the feasibility of this study will primarily be descriptive in terms of attrition rate, reasons for drop-out, and compliance with and deviations from the treatment protocol as well as a summary of the data regarding the strengths and suggestions for improvements of the treatment from the perspective of the participant.

Potential participation bias will be explored by not only comparing relatives who volunteered to participate in the study to those who refused to be in the study with respect to sociodemographic variables, but also by comparing the mean scores of PCBD, MDD, and PTSD.

##### Data analyses

Within-subjects repeated measures ANOVA with time (baseline, 1, 12, and 24 weeks post-treatment) as the repeated measure will be performed to evaluate the effects of the treatment in terms of changes in mean scores of PCBD.

Between-subjects multivariate analysis of covariance (MANCOVA) will be performed to compare changes in PCBD, MDD, PTSDD, and mindfulness scores between the treatment and waiting list condition. Specifically, scores at post-treatment (in the treatment condition) and post-waiting period (in the waiting list condition) on measures tapping these phenomena will be compared, including baseline scores as covariates.

Within-subjects MANCOVA with time (baseline, 1, 12, and 24 weeks post-treatment) as the repeated measure will be performed to evaluate the short- and long-term effects of the treatment in terms of change in mean scores of PCBD, MDD, PTSD, and mindfulness. To test whether the treatment effect is mediated by changes in cognitive variables (i.e., grief cognitions, intrusive memories, rumination, and repetitive negative thinking), behavioural variables (i.e., avoidance behaviour), and self-compassion, only the scores of measures tapping these constructs that show the strongest association (based on univariate analyses) will be added to a multiple regression model. Finally, to assess the potential change at micro-level in repetitive negative thinking, intrusive memories and self-compassion throughout the course of the treatment a within-subjects repeated measures ANOVA with time (session 1 to session 8) as the repeated measure will be performed with mean scores of measures tapping repetitive negative thinking, intrusive memories, and self-compassion as outcome measures.

Data will be analysed according to the intention-to-treat principle. Missing data will be handled using multiple imputations. The Statistical Package for the Social Sciences will be used for the analysis. The small sample size of the pilot RCT increases the risk of type II error; the preliminary results regarding the potential effectiveness will therefore be reported with caution following the recommendations for conducting a pilot study [78].

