**Methods:**

A pilot RCT comparing participants of the CBT condition (*n* = 15) with waiting list controls (*n* = 15) will be executed. Individuals suffering from psychopathology related to the long-term disappearance of a loved one are eligible to participate. The treatment consists of eight individual sessions. Questionnaires tapping psychological constructs will be administered before, during, and after the treatment. The feasibility of the treatment will be evaluated using descriptive statistics (e.g., attrition rate). The primary analysis consists of a within-group analysis of changes in mean scores of persistent complex bereavement disorder from baseline to immediately post-treatment and follow-up (12 and 24 weeks post-treatment).

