### Study objectives

The aim of this pilot study is to evaluate the feasibility and the potential effectiveness of CBT with elements of mindfulness in reducing PCBD, MDD, and PTSD symptoms and enhancing the extent of mindfulness among relatives of missing persons. Based on previous studies, we expect that the treatment effect will be mediated by changes in negative cognitive and behavioural variables plus enhancement of self-compassion.

The feasibility of the pilot RCT will be explored by the evaluation of the (1) specifics of potential participation bias, (2) attrition rate, (3) methods used and study design, (4) treatment fidelity, and (5) strengths and suggestions for improvements of the treatment from the perspective of the participant. The primary objective of the analysis of the pilot RCT is to assess changes in mean scores on a measure of PCBD from baseline to 1, 12, and 24 weeks post-treatment. A within-group instead of a between-groups analysis will be executed because this will give the most rigorous information about the potential effects of this treatment given the small sample size.

Secondary objectives of the analysis of the pilot RCT are (1) to evaluate whether the mean scores on measures tapping PCBD, MDD, PTSD, and mindfulness of the treatment group differ from the waiting list control group at the post-treatment/post-waiting period assessment when adjusting for the baseline scores and (2) to test whether the treatment effect is mediated by changes in negative cognitive variables (i.e., reductions in negative grief cognitions, intrusive memories, rumination, and repetitive negative thinking) and behavioural variables (i.e., avoidance behaviours) and enhancement of self-compassion. In addition, the extent of change in repetitive negative thinking, intrusive memories, and self-compassion in response to the treatment will be explored at micro-level by means of tracking measures tapping these constructs during the treatment.

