### Sample size

To find a within-subjects difference in PCBD symptom across four time points (baseline and 1, 12, and 24 weeks post-treatment) of medium effect size [19] with a power of 80 %, an *α* of 0.05, assuming the correlation between the measures to be 0.50, a sample size of in total 24 participants is sufficient. By taking into account a drop-out rate of 19 %, based on a review that reported a mean attrition rate of 19 % among studies that evaluated the effectiveness of CBT for bereavement-related psychopathology [19], a total sample size of 29 is required.

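### The primary question is change in grief score from baseline to 1, 12 and 24 weeks, but the stated test and the sample size rest on one non-directional four-occasion time effect that identifies no visit

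*Protocol article*

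**What the plan says.** The Study objectives section gives the primary objective of the analysis as "to assess changes in mean scores on a measure of PCBD from baseline to 1, 12, and 24 weeks post-treatment". The Methods paragraph of the abstract describes the primary analysis in the same terms: a "within-group analysis of changes in mean scores of persistent complex bereavement disorder from baseline to immediately post-treatment and follow-up", with follow-up at 12 and 24 weeks.

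The Data analyses section names one test for this, with the PCBD score as outcome: "Within-subjects repeated measures ANOVA with time (baseline, 1, 12, and 24 weeks post-treatment) as the repeated measure will be performed to evaluate the effects". PCBD also enters two multivariate analyses in that section:
- A within-subjects MANCOVA with the same four-level time factor, intended "to evaluate the short- and long-term effects of the treatment in terms of change in mean scores of PCBD, MDD, PTSD, and mindfulness".
- A between-group MANCOVA at post-treatment or post-waiting, adjusted for baseline.

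The Sample size section is built on a "within-subjects difference in PCBD symptom across four time points (baseline and 1, 12, and 24 weeks post-treatment"), with a medium effect, 80% power, α 0.05 and correlation 0.50. It gives 24 evaluable participants, or 29 after allowing for 19% drop-out. The article names no contrast of baseline with a particular visit.

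**The concern.** The objective is about changes from baseline at three horizons. The time effect of a four-level repeated measures ANOVA has as its null that all four means are equal. It has 3 degrees of freedom and no sign. Rejection means that some occasion, or some combination of occasions, differs from the others. The null for one visit, such as 24-week mean equal to baseline mean, can be true while the time effect is significant, because of a temporary fall at 1 week. A significant result is also compatible with deterioration.

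The multivariate analyses do not fill the gap. The within-subjects MANCOVA is again an overall test over the same four occasions, although it is meant to address both short- and long-term effects. The between-group MANCOVA covers only the first post-treatment point.

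Two things are at stake. A significant time effect could be read as evidence of lasting benefit when it carries no such information. And if the hoped-for pattern is a sustained drop, the overall test spends degrees of freedom on differences among the three later visits and so loses power against a contrast aimed at baseline.

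**Working it through.** **Inputs.** From the Sample size section: 24 evaluable participants, m = 4 occasions, ρ = 0.50, α = 0.05, power 80%, medium effect. Assumptions: medium means Cohen's f = 0.25, sphericity holds, and the SD is 1 at every occasion.

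**1. Reproduce the plan's figure.** The noncentrality is λ = N·m·f²/(1 − ρ) = 24 × 4 × 0.0625/0.5 = 12, with 3 and 69 df. Power is 81.7%; N = 23 gives 79.7%. The smallest N for 80% power is therefore 24, as stated. With f = 0.20 the requirement would be 36, and with f = 0.30 it would be 17, so f = 0.25 is the reading that fits. It also shows that the trial is sized on the overall time effect.

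**2. What that effect size means at one occasion.** λ depends on the means only through SS, the sum of squared deviations of the four means from their average. The order is baseline, 1, 12, 24 weeks.
- Sustained drop (0, −d, −d, −d): SS = (0.75d)² + 3(0.25d)² = 0.75d².
- Drop at 1 week only (0, −d, 0, 0): SS = 0.75d².
- Worsening at 24 weeks only (0, 0, 0, +d): SS = 0.75d².

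Setting SS = 4f² = 0.25 gives d = √(0.25/0.75) = 0.577 SD.

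**3. Rejection rate of the time effect.** The three patterns have the same SS, so they have the same power, 81.7%. Simulation (40,000 trials each) gives 81.5%, 81.7% and 81.9%. A worsening of 0.5 SD at both 12 and 24 weeks has SS = d² = 0.25 and gives 81.8%.

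**4. Range.** At d = 0.5 SD, SS = 0.1875, λ = 24 × 0.1875/0.5 = 9 and power is 68%. At f = 0.25 with a sphericity epsilon of 0.7, power is about 70%. With ρ = 0.3 it is 66%, and with ρ = 0.7 it is 97%. With 29 analysed it is 89% at 0.577 SD and 78% at 0.5 SD. In every case the rate is the same for the three patterns in step 2.

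**5. Contrasts with single visits, n = 24.** The SD of a change is √(2(1 − 0.5)) = 1, so the t noncentrality is d√24: 2.83 at 0.577 SD and 2.45 at 0.5 SD.

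| Change at the visit | Unadjusted 0.05 | Bonferroni 0.05/3 |
|---|---|---|
| 0.577 SD | 77% | 60% |
| 0.5 SD | 65% | 46% |

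When the drop is at 1 week only, the nulls at 12 and 24 weeks are true, and the unadjusted contrasts there reject about 5% of the time each.

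**6. Baseline versus the mean of the three later scores.** The variance of the mean of three scores is (1 + 2 × 0.5)/3 = 2/3. The variance of the contrast is 1 + 2/3 − 2 × 0.5 = 2/3, SD 0.816.
- Sustained 0.577 SD: noncentrality 0.577/0.816 × √24 = 3.46, power 91% (time effect 82%).
- Sustained 0.5 SD: noncentrality 3.00, power 82% (time effect 68%).
- Drop of 0.577 SD at 1 week only: the contrast is 0.577/3 = 0.192, noncentrality 1.15, power about 20%.

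**The case against.** The article condenses a fuller plan. It names a model and does not exclude contrasts, which come readily from the same ANOVA and are often specified in an analysis plan that is not shown here. The objective does not use the word each, and one question about the overall course is a possible reading. The wording about short- and long-term effects belongs to the multi-outcome MANCOVA, not to the primary ANOVA sentence. This is a pilot whose results are to be reported with caution, and the four means would reveal a relapse or a worsening. The short-term effect also has a controlled comparison.

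Much of this stands, and it limits the point in three ways.
- A reader might infer that the plan rules out visit contrasts. It does not say so. The point is that the document ties its stated primary test and its power basis to the overall time effect, which does not match the objective it states.
- A reader might take 82% as a false-positive rate. It is not. In the relapse and worsening patterns the four means do differ, so rejecting equality is correct. What fails is the step from that rejection to a statement about benefit at a given visit. The equal rates follow from equal spread of the means, and the level depends on the assumed effect.
- A reader might infer that the trial will announce a 24-week benefit from p < 0.05. The article contains no such success rule.

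The promised caution does not close the gap, because the article links it to type II error, whereas the difficulty here is what a positive result means.

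**Conclusion.** The point holds as a mismatch between the primary objective and the test and sample size stated for it. The time effect is non-directional and does not locate a change. At the planning effect it rejects about 82% of the time whether the benefit lasts, has gone by 12 and 24 weeks, or scores only worsen at 24 weeks. That figure assumes f = 0.25, 24 analysed, ρ = 0.50 and sphericity; at a 0.5 SD shift it is 68%. The mismatch itself does not depend on these assumptions. Visit means would show the pattern descriptively, so the consequence is limited: a significant time effect alone would not support a claim of benefit at 12 or 24 weeks, and for a sustained drop it is less powerful than a contrast of baseline with the later scores.

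**What to change.** Using the same repeated-measures data:
- Plan contrasts of baseline with 1, 12 and 24 weeks, each reported as mean change with a 95% CI. Base any short- or long-term statement on the contrast for that visit, and do the same for the secondary outcomes.
- If a single overall test is wanted, use baseline versus the mean of the three later scores. Keep the overall F as description.
- Do not make the visit contrasts conditional on the pooled contrast. With pooled, then 1, 12 and 24 weeks in fixed order, simulation at n = 24 gives a 56% chance of reaching a 24-week claim under a sustained 0.577 SD drop (40% at 0.5 SD). A true benefit at 1 week only would pass the first step about 20% of the time.

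The cost is wording: no new data and no extra participants. The downside is precision. At n = 24 each visit contrast has 77% power at 0.577 SD and 65% at 0.5 SD unadjusted, or 60% and 46% with Bonferroni over three visits. For 80% power per unadjusted contrast, 26 evaluable would be needed at 0.577 SD and 34 at 0.5 SD. The visit contrasts are therefore best presented mainly as estimates with intervals, which suits the pilot aim.
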